### 2.4. Primary and secondary objectives

Primary objectives: HIPEC effectiveness in the combined treatment of rmhTNF-NC in abdominal effusion caused by advanced OC will be analyzed. The response will evaluated according to the WHO criteria^[9]^ and will classify as complete response (CR): the abdominal effusion disappeared completely and lasted for more than 4 weeks, partial response (PR): more than 50% less effusion than before treatment (based on the maximum depth of effusion observed by B-ultrasound examination), stable disease (SD): fluid accumulation should be reduced by less than 50% or increased by less than 25% from before treatment (based on the maximum depth of fluid accumulation observed by B-ultrasound examination), and progressive disease (PD): Fluid accumulation increased by more than 25% compared with before treatment. Objective response rate (ORR) calculated by CR + PR. Disease control rate (DCR) calculated by CR + PR + SD. The evaluation of adverse reactions was divided into grade 0 to 4 according to NCI CT CAE 4.0.

Secondary objective: Quality of life (QoL), QoL was assessed with the European Organization for Research and Treatment for Cancer Quality of Life Questionnaire core 30 (EORCT QLQ-C30) by the dietician before HIPEC and 1 month after HIPEC.

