### 2.5. Statistical analysis

SAS 9.4 statistical analysis software is used for calculation. Full analysis set (FAS) refers to the case that has used the research drug at least once and has at least 1 main index measurement data after treatment. For the case data of failure to observe the whole treatment process, the last observation data is used to carry forward to the final result last observation carried forward (LOCF) of the study. Cases never using the drug of this study will be excluded. Per Protocol Set (PPS) refers to the case that meet the inclusion criteria, do not meet the exclusion criteria, have valid baseline values, have good compliance, and do not violate the clinical trial protocol (e.g., do not use prohibited drugs, etc), on the basis of the FAS. Safety Set (SS) refers to the case that has used the study drug at least once after enrollment and have a record of safety indicators. Both the full analysis set and the protocol set were used in the efficacy analysis, and FAS results were the main results. Security analysis uses security data sets. The statistical or grade data is compared by *χ*^2^ test and two-category Logistic multiple regression (Enter method) to analyze the factors affecting the objective curative effects. *P* < 0.05 are considered as statistically significant difference.

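### With a single post-treatment QLQ-C30 assessment, LOCF applied to quality of life can only insert the baseline score, so FAS patients without a month-1 form count as exactly unchanged

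*Protocol article*

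**What the plan says.** Section 2.4 names quality of life as its only secondary objective: "Secondary objective: Quality of life (QoL), QoL was assessed with the European Organization for Research and Treatment for Cancer Quality of Life Questionnaire". The questionnaire is completed "by the dietician before HIPEC and 1 month after HIPEC", which is one baseline score and one post-treatment score. The abstract gives a different list of secondary outcomes, progression-free survival and adverse events, without quality of life.

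Section 2.5 has one rule for incomplete data. Its trigger is "For the case data of failure to observe the whole treatment process", and its action is that "the last observation data is used to carry forward to the final result last observation carried forward (LOCF) of the study". No endpoint is named or exempted, and nothing is said about death or about patients who have only a baseline value.

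To enter the FAS, a patient must be one who "has used the research drug at least once and has at least 1 main index measurement data after treatment". On the analysis sets: "Both the full analysis set and the protocol set were used in the efficacy analysis, and FAS results were the main results".

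The main index is not settled. Section 2.4 gives the primary objective as "HIPEC effectiveness in the combined treatment of rmhTNF-NC in abdominal effusion caused by advanced OC will be analyzed", judged by ultrasound depth. The abstract gives one-year overall survival as the primary outcome. Section 2.3 lists abdominal ultrasound monthly to one year. Section 2.1 sets enrolment at 20 patients.

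**The concern.** LOCF is usually defended on the ground that the last value seen on treatment says something about the value that was missed. That defence is at least available for effusion depth, which is scanned repeatedly after treatment. It is not available for quality of life. With two time points, no post-treatment information exists to carry, and the imputed change is a constant fixed by the schedule.

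The population has advanced cancer with symptomatic ascites of at least moderate amount (Table 1). A form missing at one month because of illness, toxicity or withdrawal more plausibly hides a worse score than an identical one. Imputing zero would then move the mean change in the favourable direction. The repeated zeros would also reduce the standard error without adding any data. The FAS entry condition does not prevent this, because it asks for a post-treatment value of the main index and not of the QLQ-C30. A patient with one post-treatment scan and no questionnaire is in the FAS.

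At stake is the secondary objective of section 2.4. The Conclusion also names better quality of life among the benefits that the follow-on randomised trial is expected to support.

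**Working it through.** The plan states no quality-of-life effect size, power or dropout rate, so it has no figure to reproduce. The check is one step of logic and then arithmetic on stated assumptions.

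**Step 1: what LOCF can carry.** The assessment times are {baseline, month 1}. If month 1 is missing, the only earlier value is the baseline. Imputed change = baseline − baseline = 0 for every such patient.

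**Step 2: bias in the mean change.** Let N be the patients analysed, k those without a month-1 form, d the completers' mean change (positive means better) and D the unseen worsening in those missing.

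- LOCF mean = (N − k)d / N
- Mean counting the worsening = [(N − k)d − kD] / N
- Bias = difference = (k/N) × D

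N = 20 is from section 2.1 and assumes that everyone enters the FAS. The values of k and D are assumptions; the document gives neither.

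| k | D = 10 | D = 20 | D = 30 |
|---|---|---|---|
| 2 | 1.0 | 2.0 | 3.0 |
| 3 | 1.5 | 3.0 | 4.5 |
| 4 | 2.0 | 4.0 | 6.0 |
| 5 | 2.5 | 5.0 | 7.5 |

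If those missing truly did not change (D = 0), the bias is 0.

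**Step 3: effect on the standard error.** Assume 16 completers with mean +10 and SD 20, and 4 patients missing who truly worsened by 20. The completers' sum of squares about their own mean is 15 × 400 = 6000.

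- LOCF: mean = (16 × 10 + 4 × 0)/20 = 8.0. Sum of squares = 6000 + 16 × 2² + 4 × 8² = 6320. SD = √(6320/19) = 18.24, SE = 18.24/√20 = 4.08, one-sample t-test p = 0.065.
- Worsening counted: mean = (160 − 80)/20 = 4.0. Sum of squares = 6000 + 16 × 6² + 4 × 24² = 8880. SD = 21.62, SE = 4.83, p = 0.42.
- Completers only: mean 10.0, SE = 20/√16 = 5.0, p = 0.064.

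LOCF has the smallest SE of the three because four identical zeros are treated as data. The article does not specify this t-test; it is used here only to show the size of the effect.

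**Step 4: completers only is not a remedy.** Its bias is d − [(N − k)d − kD]/N = (k/N)(d + D) = 0.2 × 30 = 6.0 points in the example, against 4.0 for LOCF. Whenever completers improve on average, their mean alone lies further from the target than the LOCF mean does.

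**Step 5: early deaths.** Take a patient who dies before any post-treatment scan. If the main index is effusion (section 2.4), the patient has no post-treatment value, is outside the FAS and drops out of the quality-of-life result. If it is overall survival (abstract), the survival record may keep the patient in the FAS, and the baseline score is carried. By either route the death does not appear as a poor quality-of-life outcome.

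**The case against.** Four objections deserve an answer.

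1. A reader might infer that every patient who dies or deteriorates within the month is recorded as unchanged. The text does not support that. Patients who deteriorate and still complete the form are scored as observed. If effusion is the main index, early deaths without a scan leave the FAS and receive no imputed value. Only FAS patients without a month-1 score are affected.

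2. Section 2.5 does not expressly apply LOCF to quality of life. Its trigger concerns the treatment course, and the treatment steps in section 2.2 run from day 1 to day 7, so a patient who finishes treatment and later misses the questionnaire may not be covered. This stands as an ambiguity. But the rule exempts nothing and carries data to the study's final result, so applying it to the QLQ-C30 is a natural reading and the text should exclude it.

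3. The size rests on assumed k and D and on a mean-change analysis that the article does not specify. That also stands. Entry requires ECOG of at most 1, so few forms may be missing, and the low end of the range is 1 point. For a patient who died, no month-1 score exists and D is undefined. How quality of life is analysed may properly be left to a fuller document. The point here is a stated rule that suits this endpoint badly, not an analysis that was left out.

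4. In the worked example LOCF is closer to the assumed truth than completers only, and no version reaches p < 0.05. Both statements are correct. The example therefore does not show that LOCF creates significance, and simply dropping LOCF in favour of the observed mean would not be an improvement. Early toxicity is also captured separately, through graded adverse reactions analysed in the Safety Set.

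**Conclusion.** The point holds in a limited form. Where the LOCF rule is applied to the QLQ-C30, it can only insert the baseline score, so FAS patients without a month-1 questionnaire count as exactly unchanged. This follows from the schedule and needs no assumption.

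The direction and size do need assumptions. If forms are missing because of deterioration, the mean change is too favourable by (k/N) × D. That is 1 to 7.5 points for N = 20, k = 2 to 5 and D = 10 to 30, and zero if those missing did not change. The standard error is also too small: 4.08 against 4.83 in the example. Early deaths are lost from the result as poor outcomes by one of two routes, and the document does not settle which.

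It would go too far to say that the plan scores all early deaths and deteriorations as no change, or that the reported benefit will double. The doubling from 4.0 to 8.0 belongs to one chosen set of inputs. For a secondary objective in an exploratory 20-patient single-arm study, this is a correction worth making but not one that threatens the trial.

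**What to change.** In section 2.5:

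- State that LOCF does not apply to the QLQ-C30.
- Report the number of patients improved at 1 month, on a named scale and by a threshold fixed in advance, out of all treated patients. Count death or a missing form as not improved. Using all treated patients, not the FAS, keeps early deaths in the denominator whichever main index is meant.
- Give the observed paired change descriptively, with the number of missing forms and the reason for each, and list deaths separately.
- Add a sensitivity analysis that assumes worsening in those missing, for example over the 10 to 30 point range used above, so that the completers' mean does not stand alone.

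The cost is a few sentences and no new data beyond recording why a form is missing. The downside is that the quality-of-life figure may look less favourable, and a form missed for a purely administrative reason will count against the treatment.

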### 2.5. Statistical analysis

SAS 9.4 statistical analysis software is used for calculation. Full analysis set (FAS) refers to the case that has used the research drug at least once and has at least 1 main index measurement data after treatment. For the case data of failure to observe the whole treatment process, the last observation data is used to carry forward to the final result last observation carried forward (LOCF) of the study. Cases never using the drug of this study will be excluded. Per Protocol Set (PPS) refers to the case that meet the inclusion criteria, do not meet the exclusion criteria, have valid baseline values, have good compliance, and do not violate the clinical trial protocol (e.g., do not use prohibited drugs, etc), on the basis of the FAS. Safety Set (SS) refers to the case that has used the study drug at least once after enrollment and have a record of safety indicators. Both the full analysis set and the protocol set were used in the efficacy analysis, and FAS results were the main results. Security analysis uses security data sets. The statistical or grade data is compared by *χ*^2^ test and two-category Logistic multiple regression (Enter method) to analyze the factors affecting the objective curative effects. *P* < 0.05 are considered as statistically significant difference.

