### 2.1. Start trial

Inclusion, treatments started in Zhongshan Affiliated Hospital, Guangzhou University of Chinese Medicine by the end of 2021. Twenty patients will be enrolled in this trial.

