### 2.2. Therapeutic method

After ascites was extracted as far as possible, the patients were treated by HIPEC combined with intracavity injection of rmhTNF-NC. The specific treatment methods were as follows: d1 and d4 were given cisplatin at a dose of 30 mg/m^2^, and the cisplatin and 2000 to 3000 mL 0.9% normal saline were added into a special treatment bag for body cavity thermoperfusion chemotherapy, and then the air in the bag was drained. The treatment bag was connected with the coelomic thermal perfusion therapy machine. After the liquid medicine in the treatment bag was heated to 43 °C, the machine was connected with the abdominal drainage catheter placed in the patient, and the coelomic circulation thermal perfusion therapy was carried out on the patient. D7 was mixed with 20 mL 0.9% normal saline, 10 mg dexamethasone and 3 million IU rmhTNF-NC, and injected into the abdominal cavity through abdominal drainage catheter. Between 2 and 4 hours after the infusion, the patient was asked to change his position every 15 minutes so that the solution was evenly distributed in his abdominal cavity.

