### 2.3. Follow-up

During follow-up before and after the completion of HIPEC, physical examinations and measurements of white blood cell count, Hemoglobin, neutrophil count, blood platelet count, liver enzymes and serum creatinine levels were performed and then every 1 month for abdominal ultrasonography until the one-year point.

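### The main efficacy set leaves out treated patients who have no post-treatment measurement, which pushes the response rate upward in a 20-patient single-arm trial

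*Protocol article*

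**What the plan says.** All the population definitions are in section 2.5 of the protocol article.

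- **FAS.** A case enters if it "has used the research drug at least once and has at least 1 main index measurement data after treatment". For efficacy, "FAS results were the main results". The per-protocol set is a subset of the FAS.
- **Missing data.** For patients not observed through the whole treatment course, "the last observation data is used to carry forward to the final result last observation carried forward (LOCF) of the study".
- **Safety Set.** A case enters if it "has used the study drug at least once after enrollment and have a record of safety indicators".
- **Exclusion.** "Cases never using the drug of this study will be excluded".

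Section 2.4 defines response by change in effusion depth on ultrasound, in four categories: complete response, partial response, stable and progressive disease. ORR is the first two and DCR the first three. There is no category for patients who cannot be evaluated.

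Section 2.3 schedules ultrasound "every 1 month for abdominal ultrasonography until the one-year point", and examinations and blood tests before and after HIPEC. Section 2.2 gives cisplatin HIPEC on d1 and d4 and rmhTNF-NC on D7. Section 2.1 sets the size: "Twenty patients will be enrolled in this trial".

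**The concern.** Entry to the main efficacy set depends on something that happens after treatment begins. Eligible patients have peritoneal malignancy with symptomatic ascites of at least moderate amount (Table 1), and the only stated scan interval is monthly. A patient may therefore be treated and lost before any post-treatment scan. Loss through death, deterioration or withdrawal is plausibly linked to poor response.

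The title calls the trial randomized, but the Design section describes a single-arm study and only one regimen is set out. With no comparator, an error in the denominator passes straight into the estimate. Section 4 announces a multicenter randomized trial to follow, so an inflated ORR could also feed the planning of that trial.

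**Working it through.** **1. Can an unscanned patient get back in?** Take a patient who starts HIPEC on d1 and has no later ultrasound, with ultrasound response as the main index.

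- FAS: out, because there is no post-treatment main-index value.
- Last observation carried forward: no help. There is no post-treatment value to carry, and the patient is already outside the set.
- Per-protocol set: out, because it is built on the FAS.
- Response definitions in section 2.4: no rule assigns the patient to non-response.

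No efficacy set keeps this patient.

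**2. Size for ORR.** The plan's only planning figure is 20 patients. It comes with no target rate, power or expected loss, so there is nothing to reproduce. The size has to be shown on assumptions.

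- n = 20 treated (section 2.1).
- x = responders, all of them scanned. Assumption: 9, because the ORR cited in section 3 for malignant abdominal effusion is 46.03% and 0.4603 × 20 = 9.2. A second value of 12 is shown for range.
- k = treated patients with no post-treatment scan. Assumption: 1 to 3.

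With every treated patient counted, ORR = x/n. Under the FAS, ORR = x/(n − k). The difference is xk/[n(n − k)].

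| k | x = 9: FAS, against 9/20 = 45.0% | x = 12: FAS, against 12/20 = 60.0% |
|---|---|---|
| 1 | 9/19 = 47.4% (+2.4 points) | 12/19 = 63.2% (+3.2) |
| 2 | 9/18 = 50.0% (+5.0) | 12/18 = 66.7% (+6.7) |
| 3 | 9/17 = 52.9% (+7.9) | 12/17 = 70.6% (+10.6) |

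The same formula applies to DCR, with x the number of patients whose effusion is controlled.

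**3. Which k is plausible?** The phase IV study of rmhTNF-NC cited in section 3 involved 985 patients and reported ORR for 916. The gap is (985 − 916)/985 = 69/985 = 7.0%. If that rate applied here:

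- expected loss: 20 × 0.070 = 1.4 patients
- P(at least 1) = 1 − (1 − 0.070)^20 = 77%
- P(at least 2) = 41% and P(at least 3) = 16%, from the same binomial distribution

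So 1 or 2 is the working range and 3 is pessimistic.

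**4. Direction.** Leaving unscanned patients out amounts to assuming that they respond as often as the scanned ones. With x = 9 and k = 2, the ORR among all treated lies between 9/20 = 45.0% (neither responded) and 11/20 = 55.0% (both did). The FAS figure is 50.0%. It is too high whenever the unscanned respond less often than the scanned, which is the expected direction when death or deterioration causes the loss.

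**5. Safety Set.** Here the condition is a record of safety indicators, a term that the article does not define. A recorded death, adverse event or toxicity stop is naturally such a record, and section 2.3 adds blood tests. A treated patient can drop out in three ways only:

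- nothing about safety was recorded;
- the term is read narrowly, for example as post-treatment laboratory values;
- the study drug is read as rmhTNF-NC alone, so that a patient lost between d1 and D7 counts as never treated.

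The third reading would also remove the patient from the FAS. Section 2.5 speaks of the drug in the singular and does not say which component it means.

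**The case against.** - **Convention.** Requiring one post-baseline value is common in defining a full analysis set, and this study is exploratory. True, but the convention does not remove the bias, and a single arm has nothing to offset it.
- **The main index is not named.** The abstract gives one-year overall survival as the primary outcome. If that is the main index, a recorded early death may itself be main-index data, and the patient stays in. This stands. The point therefore rests on the ultrasound reading, which section 2.4 makes the likelier one for ORR and DCR.
- **Not every early failure leaves.** A patient whose effusion grows and who is scanned is classed as progressive disease and stays in the FAS. Some patients may miss scans for administrative reasons. Both are correct, so the point covers only treated patients with no measurement.
- **The shift is small beside the sampling error.** The exact 95% interval for 9/20 is 23.1% to 68.5%, and the article states no threshold that the shift would cross. This is fair on size. But the interval does not account for a shift in one direction.
- **The 7% is borrowed.** The article does not say why 69 patients lack a reported ORR, so the figure gives scale and shows nothing about mechanism. Table 1 also limits entry to ECOG 1 or better and excludes unstable patients, which argues against heavy early loss.

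A reader might go further and infer that early failures and deaths vanish from the safety denominator too, so that toxicity is understated. The article does not support that as a general statement: those events, once recorded, are safety records. The D7 route depends on reading the drug as rmhTNF-NC alone, while the abstract and section 2.2 present HIPEC with cisplatin and rmhTNF-NC as one combined treatment.

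**Conclusion.** The point holds for the FAS. As written, the main ORR and DCR exclude treated patients with no post-treatment measurement, and no other rule in the article recovers them. On 9 assumed responders of 20, the upward shift is 2.4 to 5.0 points for 1 or 2 unscanned patients and 7.9 points for 3. This assumes that the main index is ultrasound response and that the unscanned patients did not respond. The number of responders and the number lost are illustrations, since the article gives neither.

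Losses of a quarter of the patients, which would give 9/15 = 60.0%, might be inferred as a headline risk. Nothing in the article supports a rate that high.

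For the Safety Set, the conclusion is limited to two undefined terms and an unnecessary condition. These can drop a treated patient in the three ways listed, but need not.

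**What to change.** In section 2.5:

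1. Define the FAS as all patients who start any component of study treatment, from HIPEC on d1, with no condition on later data.
2. Count a patient with no post-treatment assessment as a non-responder for ORR and as not controlled for DCR.
3. Keep the present FAS as a response-evaluable sensitivity set. This also preserves comparison with rates reported on evaluable patients.
4. Define the Safety Set as all patients who receive any component of study treatment, with no condition on later records.
5. Use one term for study treatment throughout, covering both components, and name the main index.

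The change is a few sentences of analysis text. It needs no extra patients, visits or data. The cost is a slightly lower reported ORR, and some understatement if an unscanned patient had in fact responded. The sensitivity set will show how much the result depends on this.

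### LOCF in the main efficacy analysis can count patients who leave or die after one early partial response as responders, and the FAS definition drops those never scanned

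*Protocol article*

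**What the plan says.** Section 2.5 of the protocol article sets the missing-data rule. It covers patients described as "For the case data of failure to observe the whole treatment process"; for them, "the last observation data is used to carry forward to the final result last observation carried forward (LOCF) of the study". Death, progression and withdrawal are not treated separately. The time point that counts as the final result is not given.

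The same section limits the FAS to a patient who "has used the research drug at least once and has at least 1 main index measurement data after treatment". It also states that "FAS results were the main results", with the per-protocol set analysed alongside.

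Three other places determine what LOCF would carry:

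- **Section 2.2, drainage.** The course begins "After ascites was extracted as far as possible", so depth is reduced mechanically before the first perfusion.
- **Section 2.4, response.** The definitions include "partial response (PR): more than 50% less effusion than before treatment", judged on maximum ultrasound depth. No minimum duration is set for PR, and the text does not say whether the pre-treatment scan comes before or after drainage. Complete response (CR) does carry a duration: "the abdominal effusion disappeared completely and lasted for more than 4 weeks". ORR is CR plus PR, and the disease control rate (DCR) adds stable disease (SD).
- **Section 2.3, scans.** Abdominal ultrasound is monthly up to one year. None is explicitly scheduled between day 1 and day 7.

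**The concern.** LOCF assumes that the last value seen is a fair stand-in for the value not seen. That is doubtful for malignant ascites. Fluid is removed at the start and can re-accumulate if treatment fails, and in advanced cancer the patients who leave early are plausibly those who are failing. What happens after they leave is not observed. If their last scan was at PR level, the rule reports them as responders; if it was SD, it reports them as controlled.

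The rule also sits badly with the CR definition. One scan carried forward cannot show that the effusion stayed away for more than 4 weeks.

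The study has a single arm, so no control group shares the error. The affected result is the one declared to be the main efficacy result.

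**Working it through.** **Plan's own figure.** The only stated figure is the sample size of 20 (section 2.1). No target rate, null rate or dropout allowance accompanies it, so there is nothing to reproduce.

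**Inputs**

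- From the article: n = 20. The cited phase IV monotherapy trial had an ORR of 46.03% in abdominal effusion (Discussion, section on rmhTNF-NC). It is used here only as an illustrative completer response rate.
- Assumed: k = 2, 4 or 6 early leavers out of 20, all with at least one post-treatment scan so that they stay in the FAS.

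**Step 1. Expected ORR under the two rules**

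- Leavers as non-responders: (20 − k) × 0.4603 / 20
- All leavers carried as PR (worst case): [(20 − k) × 0.4603 + k] / 20

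| k | Non-responders | All carried as PR | Gap |
|---|---|---|---|
| 2 | 8.2854/20 = 41.4% | 10.2854/20 = 51.4% | 10 points |
| 4 | 7.3648/20 = 36.8% | 11.3648/20 = 56.8% | 20 points |
| 6 | 6.4442/20 = 32.2% | 12.4442/20 = 62.2% | 30 points |

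The gap is k/20, or 5 points per patient. With k = 4 the estimate moves from below the cited 46.03% to above it. In whole patients that is 7/20 (35%, exact 95% CI 15.4 to 59.2%) against 11/20 (55%, 31.5 to 76.9%).

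**Step 2. A milder case.** If leavers' last scans show response at the completers' rate, LOCF gives 20 × 0.4603 / 20 = 46.0% for every k. With k = 4 that is 46.0 − 36.8 = 9.2 points above the non-responder count, instead of 20.

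**Step 3. Effect on a decision.** The plan has no success threshold. As an assumption, take 14 or more responders of 20; at a true rate of 46.03% and no leavers, the chance of this is 2.7%. With k leavers all carried as PR, the remaining 20 − k patients need only 14 − k responses. The chance becomes 6.4% (k = 2), 14.2% (k = 4) and 28.5% (k = 6).

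**Step 4. The FAS denominator.** Suppose instead that the 4 leavers had no post-treatment scan. They are then outside the FAS and nothing is carried forward. With 7 responders among the other 16, the FAS gives 7/16 = 43.8%, against 7/20 = 35% for all treated patients. This is a second upward bias with a different cause.

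**The case against.** A reader might infer that LOCF carries forward a scan taken just after drainage. The article does not support that as a fact. Scheduled ultrasound is monthly and none is placed inside the day 1 to day 7 course, so the first scheduled post-treatment scan may come about a month later, when fluid in a treatment failure has had time to return. The drainage effect needs an early or unscheduled scan and a pre-drainage baseline, and neither is specified. This limits the mechanism but does not remove the fault: a PR at month 1 followed by death is still carried.

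A reader might also infer that all dropouts and deaths become responders. They do not. A last value of SD or progressive disease stays a non-response in ORR, and progressive disease stays uncontrolled in DCR. Patients with no post-treatment scan are omitted, not carried. The size of the inflation therefore depends on what leavers' last scans show.

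The CR problem is also limited. The article does not say that LOCF overrides the CR duration, and a single clear scan could be graded PR without contradiction. Inflation of ORR therefore runs mainly through PR.

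The scope of the rule is uncertain: the whole treatment process may mean the short course or the year of follow-up. Nothing says that LOCF applies to the QLQ-C30. The abstract names one-year overall survival as the primary outcome, which LOCF on ultrasound does not touch; section 2.4, however, makes response the primary objective.

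Finally, this is a 20-patient exploratory study that also reports a per-protocol analysis. That tempers the consequences, but the FAS result is still the declared main one.

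**Conclusion.** The point stands in a limited form. The article states LOCF for the main efficacy result with no separate handling of death, progression or withdrawal, and PR has no minimum duration. An early PR (or SD, for DCR) can therefore be reported as the final outcome of a patient who then leaves or dies, and one carried scan cannot establish CR. Each PR carried in place of a non-response adds 5 points to ORR when all 20 patients are in the FAS. The range of 10 to 30 points for 2 to 6 leavers is a worst case. It rests on assumed leaver counts, on every leaver's last scan being PR, and on counting leavers as non-responders as the comparison. The 14-of-20 threshold is likewise an assumption.

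The FAS requirement for a post-treatment measurement is a separate upward bias, and removing LOCF alone would leave it in place. The documents support saying that the main result could be inflated, not that it will be.

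**What to change.** In section 2.5, with a matching line in section 2.4:

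1. Delete LOCF for response.
2. Fix the time at which response is assessed, and state whether the baseline scan precedes drainage.
3. Count any treated patient who dies, withdraws or lacks the ultrasound(s) needed to show CR or PR, as section 2.4 defines them, at that time as a non-responder in ORR and as not controlled in DCR. This adds no duration requirement to PR.
4. Keep every treated patient in the denominator of the main analysis, by removing the need for a post-treatment measurement.
5. Report the observed-case result as a sensitivity analysis.

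The cost is a few sentences and no added patients. The downside is a somewhat less favourable ORR and DCR, because some patients who leave for reasons unrelated to failure will count as non-responders; the observed-case analysis shows how much this matters.
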